### Recruitment and Examination

All phases of this trial will be carried out in the kindergarten that the children attend. The research team includes dentists and research assistants. Before conducting the trial, the whole team was trained by experienced specialists in dental public health. A calibrated and trained examiner screened the children who had written parental consent. All children were clinically examined, and those who met the inclusion criteria were selected. No dental radiograph examination was conducted. If a child has more than one caries-free primary molar, all of the molars will be included. At baseline and the semiannual follow-up examinations, clinical examination of the children will be conducted by a trained dentist who will be masked to the group assignment of the participant children. All clinical investigations will be conducted in kindergartens. The study children will lie on a bench and will be examined in the supine position. Tooth status will be assessed by careful visual inspection with a dental mirror attached to a handle with a light-emitting diode for intraoral illumination (MirrorLite, Kudos Crown Limited). A microbrush will be used to remove food debris and dental plaque that obstruct inspection. A World Health Organization CPI probe with a 0.5-mm ball tip will be used to confirm the presence of a carious cavity when necessary. Great care will be taken to avoid damaging the tooth surface during probing. The intervention will be free, and participants or kindergartens will not pay any cost for the research. After the examination, parents will receive a brief report on their children’s dental caries status.

Caries will be diagnosed at the cavitation level following the criteria recommended by the World Health Organization. Drying of the tooth surface with air blow will not be carried out in this study. An occlusal tooth surface will be recorded in one of the following categories: (1) sound, (2) caries confined to the enamel or into dentin but without cavitation, (3) cavitated dentin caries (active), (4) cavitated dentin caries (arrested), (5) filled surface, (6) extracted tooth, and (7) tooth with nonvital signs, such as abscess or fistula. The decayed, missing, and filled tooth surface (dmfs) index will be adopted for documenting dental caries experience. Oral hygiene status will be measured using the visible plaque index (VPI). The buccal and lingual surfaces of 6 index teeth (Fédération Dentaire Internationale tooth numbers 55, 51, 63, 71, 75, and 83) will be thoroughly examined. The presence or absence of visible plaque on the occlusal surface will be recorded. Black staining on each surface will be clinically observed and recorded (yes/no). A random sample of 10% of the study children will be re-examined on the same day at the baseline and follow-up examinations to evaluate intraexaminer reproducibility. The study follow-up is every 6 months. If some parents of the study children seek early professional intervention, all the sealed, restored, or extracted teeth will be recorded as study treatment failure.

### Questionnaire Survey

A parental questionnaire consisting of 3 fields (child’s information, child’s oral health–related behavior, and family information) will be administered at baseline and at the 30-month follow-up visit. It will collect information regarding the child’s oral hygiene practice, use of fluoride agents, dental visit behavior, snacking habits, parental educational level, and family income. The questionnaire will also assess parental satisfaction with their child’s oral health and dental esthetics. In the follow-up questionnaire, parents will be asked to report posttreatment complications of the assigned treatment, such as pain from the treated teeth and gingival irritation around the treated teeth.

### Random Allocation, Concealment, and Blinding

With regard to treatment group allocation and intervention, at baseline, participant children were stratified into the following 2 groups: (1) with dmfs score 0 and (2) with dmfs score >0. The children were allocated by a stratified randomization method with varying random block sizes, using a personal computer, into 1 of 3 intervention groups. The unit of treatment allocation was at the subject level. The allocation sequence was generated by a technician who was not involved in the examination and random allocation.

Regarding allocation concealment, a randomization scheme was produced, and a random code for each participant was placed in an opaque envelope. The dental team did not know the treatment allocation before the time of applying the material. The envelope was opened by a dental assistant, and then, the materials were prepared following the assigned intervention of the child according to group allocation. The children and their parents have not been informed about their group allocation. The examiner will also be blinded to the assigned intervention. However, the dentists who will provide the interventions will not be blinded because the agents (SDF, NaF, and placebo) look dissimilar in nature.

### Interventions

Occlusal molar surfaces without cavitated dentine caries lesions were randomly allocated to receive SDF, NaF varnish, or a placebo control. Clinical examinations will be conducted every 6 months after the intervention.

The treatment interventions are as follows: (1) Group A, semiannual topical application of 38% SDF solution (Saforide, Toyo Seiyaku Kasei Co, Ltd); (2) Group B, semiannual topical application of 5% NaF varnish (Duraphat, Colgate Palmolive); (3) Group C, semiannual topical application of a placebo control (tonic water).

The application procedure is as follows:

Remove food debris and dental plaque, if any, from the occlusal surface to allow good contact between the study agent and tooth surface.Isolate the occlusal surface of sound primary molars with cotton roll or gauze. For Group A, dispense 1 drop (0.05 mL) of 38% SDF solution, which contains approximately 2.2 mg fluoride ions, in a plastic dappen dish. For Group B, dispense 1 drop (0.25 mL) of 5% NaF varnish, which contains approximately 5.6 mg fluoride ions, in a plastic dappen dish. For Group C, dispense one drop (approximately 0.05 mL) of tonic water in a plastic dappen dish.Slightly bend a microapplicator, and dip it in the agent.Apply the agent with the microapplicator directly onto the occlusal surface of sound primary molars in each quadrant. One application is used for 1 quadrant (1 or 2 primary molars). If a child has 8 sound molars, he or she will receive a maximum of 4 applications on that day.Gently rub the occlusal surfaces with the microapplicator while continuing to isolate the treated teeth whenever possible and ensure that the entire occlusal surfaces are wetted by the agent.Minimize contact of the SDF solution with adjacent gingiva or mucosa to avoid potential soft-tissue irritation.

Subsequently, the study children will be instructed not to eat and drink for 30 minutes after application. The intervention will be provided every 6 months. Application of the appropriate agent (either 38% SDF, 5% NaF, or tonic water) will be carried out after an oral examination according to the assigned treatment group. The schedule of subject enrollment, interventions, and outcome assessments is shown in Figure 1.

Parents of all study children will be invited to attend an oral health talk by a dentist once a year. A presentation aided by color photographs and slides about child oral care will be given to parents in the kindergartens. A set of a toothbrush and fluoridated toothpaste will be given to all study children as a souvenir once a year. After the examination, a report on the child’s oral health status, including caries status, and leaflets about the child’s oral health will be sent to the parents.

**Figure 1 figure1:**
[figure not shown]
Schedule of subject enrollment, interventions, and outcome assessments. NaF: sodium fluoride; SDF: silver diamine fluoride.

### Outcome Measure

Information related to the outcomes of the trial will be collected at baseline and thereafter semiannually for 30 months.

#### Primary Outcome 

The treatment will be classified as “success” if an occlusal surface at baseline does not develop cavitated dentin caries lesions at the follow-up examination. “Failure” will be recorded if the surface develops cavitated dentin caries; the tooth has received dental sealant placement, a crown, or occlusal fillings; or the tooth is missing due to caries.

#### Secondary Outcomes

Parent’s satisfaction with their child’s dental health and dental appearance will be measured using a 5-point Likert scale, ranging from 1 (very dissatisfied) to 5 (very satisfied).

Information on the adverse effects of SDF treatment, such as tooth pain, gingival irritation, and systemic toxicity (eg, nausea and vomiting), will be collected through a parental questionnaire within a week after the intervention. During the follow-up examination, the examiner will look for signs and symptoms of potential side effects, including blackening of the treated teeth and adjacent teeth. Regarding parental satisfaction, questionnaires will be distributed to assess parent’s satisfaction with their child’s oral health and dental appearance before the trial and at the 30-month follow-up.

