Several strategies, including placement of dental sealant and topical application of sodium fluoride (NaF) varnish, have been proposed to prevent occlusal surface caries. Nevertheless, it is a challenge to place dental sealants in the primary molars of young children because the application is technique sensitive and requires optimum tooth isolation. NaF varnish is another potential agent for preventing dental caries, but it is not cost-effective in the context of government-funded services [10]. The relatively high cost of professionally administered fluoride varnish has hindered its widespread adoption in many countries [11]. Recently, silver diamine fluoride (SDF) has been considered a therapeutic agent for treating cavitated dental caries lesions in young children and those with special needs [12]. Several laboratory studies have documented its antibacterial effects in inhibiting cariogenic bacteria and its remineralizing effects [13]. Results of randomized clinical trials have shown its caries-arresting effects in preschool children [14-16]. No major adverse effects of SDF were observed, except dark staining on treated lesions after application [17]. A systematic review concluded that the caries arrest rate of 38% SDF was as high as 81% (95% CI 68%-89%; *P*<.001) [18]. In light of this, the American Academy of Pediatric Dentistry developed a guideline on the use of 38% SDF for arresting cavitated dentin caries lesions in primary teeth among children [12]. Recently, another systematic review and network meta-analysis concluded that semiannual application of 38% SDF solution showed the highest effectiveness for caries arrest in advanced cavitated lesions on coronal surfaces [19].

Nevertheless, clinical evidence for the dental caries–preventive effect of SDF is scarce [20]. Therefore, to fill this knowledge gap and to provide the needed clinical evidence to guide dental practice and public dental care service, this study aims to investigate the preventive effect of SDF versus NaF varnish and a placebo control on the occlusal surfaces of the primary molars of preschool children. In addition, this study will evaluate parental satisfaction with their child’s dental status and dental appearance, and the adverse effects of SDF application.

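### The one-week parent-reported adverse-effect outcome is worded for SDF only, so the prompt safety report has no stated NaF varnish or placebo comparator, and the Questionnaire Survey section gives a different scope and time

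*Protocol article*

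**What the plan says.** Four places in the protocol article bear on this.

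- **Introduction, Background.** The study will evaluate parental satisfaction "and the adverse effects of SDF application". Only SDF is named.
- **Secondary Outcomes.** "Information on the adverse effects of SDF treatment", with tooth pain, gingival irritation, nausea and vomiting as examples, "will be collected through a parental questionnaire within a week after the intervention". Only SDF is named, and the time is short. The same paragraph adds an examiner check for side effects at follow-up, which is not restricted to an arm.
- **Questionnaire Survey.** The parental questionnaire "will be administered at baseline and at the 30-month follow-up visit". In its follow-up version, "parents will be asked to report posttreatment complications of the assigned treatment". This wording covers every arm. The examples are pain and gingival irritation.
- **Random Allocation, Concealment, and Blinding.** "The children and their parents have not been informed about their group allocation", and the examiner is blinded too.

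Two further statements matter. The opening of Outcome Measure says that outcome information is collected at baseline and then every six months. Recruitment and Examination says that black staining is recorded yes/no on each surface, with no restriction by arm.

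**The concern.** Two sections word the safety outcome for SDF alone, and a third words it for all arms at a much later time. Someone following the text literally could collect one-week reports in the SDF arm and only month-30 recall in the NaF varnish and placebo arms.

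Tooth pain, sore gums and vomiting also occur in preschool children who have had no treatment. An SDF-only rate therefore cannot be attributed to SDF. One-week reports in one arm set against long recall in the others would also differ in how fully events are captured, which would probably make SDF look worse. The Discussion says that the findings should guide whether SDF enters school-based programmes, so tolerability against NaF varnish and placebo is part of what readers will want. The trial already has masked comparison arms that could supply it.

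**Working it through.** **The plan's own figures.** The document gives no figure for this outcome, so there is none to reproduce. The primary sample size is not in dispute. For 25% against 15%, two-sided 5%, Fisher's exact power is 0.9004 at the stated 351 surfaces per group. The later steps also reproduce: 1 + (6 − 1) × 0.5 = 3.5; 351 × 3.5 = 1228.5; 1228.5/6 = 204.75; 615/0.80 = 768.75. None of these changes if adverse effects are collected in all arms.

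**The sections side by side.**

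| Question | Background | Secondary Outcomes | Questionnaire Survey |
|---|---|---|---|
| Whose adverse effects? | SDF | SDF (parent report) | Any assigned treatment |
| When? | Not stated | Within a week of the intervention (parent report) | Follow-up version; the only stated time is 30 months |
| Example items | None | Tooth pain, gingival irritation, nausea, vomiting | Pain, gingival irritation |

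The scope differs between the second and third columns. The timing differs as well, unless these are two separate forms. The item lists are both open, so the missing nausea and vomiting in the third column do not show that the form omits them.

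**Which safety data have a stated comparator.**

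1. Examiner check at follow-up: yes, not limited by arm, masked examiner.
2. Black-staining record: yes, on each surface.
3. Month-30 complications item: yes, all arms.
4. One-week parent report: not stated.

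Items 1 to 3 do not replace item 4. An examination six months after an application will not show vomiting or passing gum soreness from the days after it. Assuming applications at months 0, 6, 12, 18 and 24, a month-30 item asks about events between 30 − 24 = 6 and 30 − 0 = 30 months old.

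**What a common form would give.**

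- Children per arm: 791/3 = 263.7, about 264.
- Reports per arm: 263.7 × 5 assumed applications = about 1,318. This is an upper figure for that schedule, because it assumes no dropout and every form returned.
- 95% half-width for SDF minus placebo on a child-level event proportion, with equal rates p: 1.96 × √(2p(1 − p)/n).

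| Assumed p | n = 264 | n = 211 (791 × 0.80/3, the plan's 20% dropout) |
|---|---|---|
| 1% | 1.7 points | 1.9 points |
| 3% | 2.9 points | 3.3 points |
| 5% | 3.7 points | 4.2 points |

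The rates p are assumptions; the document gives none.

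**The case against.** The strongest reply is that the SDF-only form is inferred. No section says that the one-week questionnaire goes only to SDF families. It is timed from the intervention, a word the article uses for all three agents, and SDF is the natural shorthand for the trial's safety interest. The statement that parents are not told the allocation also favours the all-arm reading. Two instruments at different times can coexist, and the general six-monthly statement does not exclude a form tied to each six-monthly application. The schedule figure is not shown here and may settle the timing.

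Much of this stands, and it rules out three stronger readings that a reader might infer:

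- *SDF safety as a whole has no concurrent control.* Not supported: the examiner check, the staining record and the month-30 item cover all arms.
- *Parents will be unmasked.* Not supported as a statement of fact. It would follow only if the one-week form went to SDF families alone or named SDF, and the document says neither. If it did happen, the parent-rated satisfaction outcome could be affected too.
- *The NaF varnish and placebo arms are asked about fewer symptoms.* Not established, because both lists give examples only.

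What the reply does not remove is the wording. The outcome is tied to SDF in two separate sections, while a third uses arm-neutral wording for a related item. This is not detail left to a fuller document: the article states whose effects are collected and when, and its statements do not agree.

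**Conclusion.** The point holds in a limited form. The prompt parent-reported adverse-effect outcome is defined for SDF only and has no stated NaF varnish or placebo comparator. Its relation to the all-arm, month-30 item is not reconciled. If the literal reading were followed, the two sources could not be compared across arms.

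This concerns a secondary outcome and leaves the primary outcome, its analysis and the sample size untouched. The plan contains no number that is wrong by a measurable amount. The size that can be given is what a common form would gain: an SDF-minus-placebo difference with a half-width of about 1.7 to 3.7 points with all children, or 1.9 to 4.2 points after 20% dropout. This rests on assumed event rates of 1% to 5%, equal arm sizes and complete returns. The recall interval of 6 to 30 months rests on the assumed five applications. If the form already goes to every arm in practice, the defect is one of wording only.

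**What to change.** 1. In Background and Secondary Outcomes, word the outcome as *adverse effects of the assigned treatment (SDF, NaF varnish or placebo)*.
2. State that one neutrally worded form, with identical items (tooth pain, gingival irritation, nausea, vomiting) and no agent named, goes to parents in all three arms within a week of each application.
3. Name that form as the source for a between-arm comparison of the proportion of children with any event.
4. Reconcile Questionnaire Survey so that the 30-month complications item is supplementary, and align the general timing statement in Outcome Measure.

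**Cost.** A wording amendment. If the form is not already given to all arms, there is also modest extra form handling and data entry at visits already scheduled. Applications already given without the form cannot be recovered, so the report should say from which visit the common form was used.

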### Sample Size Calculation

Based on previous studies [3,21], the anticipated proportion of sound occlusal surfaces at baseline developing into cavitated dentin lesions at the 30-month follow-up is approximately 25%. An absolute difference of 10% in the rate of new caries development (proportion of occlusal surfaces that develop cavitated dentin lesions at 30 months) between 2 intervention groups is considered to be clinically significant. The estimated sample size is based on the expected proportion of the development of new cavitated occlusal caries in primary molars, with the power of the study set at 90% (β=.1) and with a 2-sided test at the 5% statistical significance level. The sample size per study group, calculated by using the G*Power 3.1.9.2 software (University of Düsseldorf, Germany) is 351 sound occlusal tooth surfaces. The estimated intraclass correlation coefficient (ICC) for dental caries data at the surface level within the individual is approximately 0.5 [22]. Based on our previous survey [3], we anticipated that the mean number of sound occlusal surfaces per child would be 6 at baseline. Following the equation for the required sample size in a multilevel model, the design effect will be 3.5. Thus, the estimated sample size would be at least 1229 sound occlusal surfaces and with at least 205 children in each study group or 615 in total at baseline. The anticipated dropout rate after 30 months is 20%. Thus, 769 children in total need to be recruited at baseline. The estimated participation rate is approximately 90%, and therefore, at least 854 children have to be invited to join the study.

### Data Analysis

The collected data will be entered into a Microsoft Excel file by 2 persons, and the data will be proofread to minimize data entry error. Data will be analyzed using the SPSS software for Microsoft Windows (SPSS Inc). Intraexaminer agreement in caries diagnosis will be assessed by using Cohen kappa statistics. Since more than one molar may be selected from 1 child, multilevel data analysis will be carried out.

A chi-square test and *t* test will be performed, when appropriate, to assess the differences between groups with regard to their baseline demographic background, oral health–related behaviors, and caries experience. A chi-square test will be used to evaluate the differences in new caries development and parental satisfaction among groups. Thus, 2-level generalized estimating equation models with a logit link function (child level and surface level) will be adopted to evaluate the variables influencing the occurrence of occlusal caries at the 30-month follow-up. Independent variables include the child’s background characteristics (gender, place of birth, father’s and mother’s education levels, and family income); the child’s clinical characteristics at baseline (tooth type, such as upper or lower molars and first or second molars, presence of plaque on the occlusal surface, caries experience, and overall oral hygiene); and the child’s oral health–related behaviors (use of fluoride agents, dental visit behavior, and snacking habit). The backward elimination method will be adopted for modeling. A McNemar test will be performed to compare the differences in parent’s satisfaction with their child’s dental appearance and dental health at baseline and the 30-month follow-up. The level of statistical significance for all tests will be set at .05. An intention-to-treat (ITT) analysis will be adopted so that all study children who are randomized and all events will be accounted for in the primary analysis. The relevant government agencies have access to the collected data for the purposes of verifying the integrity of the study data and evaluating compliance with the study protocol. Regarding confidentiality, hard copies of the data will be stored in a sealed box in a locked room during the trial and after publication for 5 years. In addition, the research findings will be presented in scientific conferences for clinicians and health care researchers, and will be disseminated to the community and stakeholders through oral health educational seminars and talks.

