## Introduction

### Background

Tooth decay or dental caries is a silent epidemic. According to the Global Burden of Disease Study, dental caries in primary teeth remains a public health problem affecting more than 530 million children globally [1]. The term “early childhood caries” (ECC) has been used to describe the presence of one or more decayed, restored, or missing primary teeth in a child younger than 6 years [2]. In Hong Kong, more than half (55%) of 5-year-old children have untreated ECC, and the majority (>90%) of the decayed teeth are left untreated [3]. Children with untreated ECC may experience toothache, oral pain, and infection, leading to poor quality of life [4]. This also affects their family members’ quality of life and eventually impacts the community. Severe consequences of ECC include emergency room visits and hospitalizations with high costs of treatment, and missing school, as well as negative impacts on the ability to learn [2]. In extreme cases, untreated ECC can lead to life-threatening conditions and even death [5].

An epidemiological study found that most (78%) cases of ECC in preschool children in Mainland China involved the primary molars [6]. In Hong Kong, decayed primary molars constituted more than half (56%) of all decayed primary teeth in preschool children [7]. High prevalence of premature loss of primary molars due to untreated tooth decay has been reported [8]. Tooth decay is commonly found on the occlusal tooth surface owing to the complex anatomy of the fissure system, which makes the surface difficult to clean, thereby promoting the accumulation of a bacterial biofilm and increasing the risk of developing carious lesions [6]. In addition, young children are not able to brush their posterior teeth properly, and they may not have supervised toothbrushing during the preschool period. Hong Kong preschool children’s oral health has not improved over the last 2 decades [9]. An epidemiological dental survey in Hong Kong found that the prevalence of caries was much higher in older preschool children (38% at age 3 years and 55% at age 5 years) [3]. Currently, there is no government-subsidized dental care service for preschool children in Hong Kong.

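### The covariates named for the 30-month outcome model leave out the child's age, the one candidate for which the protocol quotes a caries gradient; the cost is small and falls on the risk-factor estimates

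*Protocol article*

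**What the plan says.** The protocol article (Data Analysis) plans generalized estimating equations with a logit link, at child and surface level, to find which variables affect occlusal caries at 30 months. It names the independent variables in three groups:

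- Background: "background characteristics (gender, place of birth, father’s and mother’s education levels, and family income".
- Baseline clinical status: tooth type, then "presence of plaque on the occlusal surface, caries experience, and overall oral hygiene".
- Behaviour: "oral health–related behaviors (use of fluoride agents, dental visit behavior, and snacking habit".

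On selection it says "The backward elimination method will be adopted for modeling". Age appears in none of the groups.

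Three other sections bear on this. Eligibility Criteria restricts entry to children aged 3 to 4. Background reports that "the prevalence of caries was much higher in older preschool children (38% at age 3 years and 55% at age 5 years". Random Allocation, Concealment, and Blinding stratifies on baseline caries experience only: "1) with dmfs score 0 and (2) with dmfs score >0".

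**The concern.** Age is the only candidate covariate for which the protocol gives a numerical caries gradient, and an age-based entry criterion means the value is held for every child. A model meant to say which characteristics drive new caries would normally contain it.

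What is at stake is mainly the interpretation of the other coefficients. Caries experience accumulates with age on the protocol's own figures, and behaviours may change with age as well. If age is not a candidate, part of its effect can be credited to variables that travel with it, and backward elimination may keep such a variable as a stand-in. Randomisation protects the treatment coefficient from this but not the risk-factor coefficients.

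**Working it through.** **Inputs from the protocol article.** Sample Size Calculation: 25% of sound surfaces cavitated at 30 months, a 10-point difference (25% against 15%), two-sided 5%, 90% power, intraclass correlation 0.5, 6 surfaces per child, 20% dropout. Background: prevalence 38% at age 3 and 55% at age 5.

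**Assumptions, not in the documents.** Half the children are aged 3 and half aged 4, and the prevalence gradient carries over to 30-month incidence on sound surfaces. Because the second is uncertain, a range is shown.

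**The plan's own figure.** Exact (Fisher) power for 25% against 15% is 0.8995 at 350 surfaces per group and 0.9004 at 351, so 351 reproduces. The design effect is 1 + (6 − 1) × 0.5 = 3.5. Then 351 × 3.5 = 1228.5, rounded up to 1229; 1228.5 / 6 = 204.75, so 205 children per group; 205 × 3 = 615; and 615 / 0.8 = 768.75, so 769. None of this depends on age adjustment.

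**Gradient.** The odds ratio from age 3 to 5 is (0.55/0.45) / (0.38/0.62) = 1.99, or √1.99 = 1.41 per year.

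**Share of variance.** The variance of a child's mean over 6 surfaces is p(1 − p) × 3.5/6, which at 25% is 0.1875 × 3.5/6 = 0.109. With two equal age groups, age contributes (p4 − p3)²/4. At an odds ratio of 1.41 and mean risk 25%, the risks are 21.8% and 28.2%, and age explains about 0.95%. At mean risk 15% it explains about 0.64%.

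**Power.** Beta-binomial simulation used 205 children per arm, 6 surfaces, intraclass correlation 0.5, 3000 runs, and a logit model with robust standard errors, fitted with and without age on the same data.

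**Confounding of caries experience.** Take prevalence 0.38 at age 3 and 0.464 at age 4 (the midpoint on the logit scale). The share aged 4 is then 0.464/0.844 = 0.550 among children with caries experience and 0.536/1.156 = 0.464 among those without. The inflation of the ratio is (1 + 0.550(R − 1)) / (1 + 0.464(R − 1)), with R the yearly age ratio. At R = 1.41 it is 1.030. This uses the odds ratio for R. The corresponding risk ratio, 28.2/21.8 = 1.29, gives about 1.02, so 3% is if anything generous.

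| Age odds ratio per year | Risk at 3 / 4 (mean 25%) | Variance explained (mean 25% / 15%) | Power without / with age | Caries-experience ratio inflated by |
|---|---|---|---|---|
| 1.20 | 23.3% / 26.7% | 0.27% / 0.18% | not run | 1.6% |
| 1.41 (quoted gradient) | 21.8% / 28.2% | 0.95% / 0.64% | 0.905 / 0.908 | 3.0% |
| 1.99 (two-year gradient in one year) | 18.6% / 31.4% | 3.7% / 2.5% | 0.907 / 0.918 | 5.9% |
| 3.00 | 15.1% / 34.9% | 8.9% / 5.8% | 0.909 / 0.928 | 8.9% |

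At 1.41 the mean standard error of the treatment coefficient is 0.1944 without age and 0.1948 with it. The coefficient moves from −0.642 to −0.645. In a logit model the small power gain comes from the slightly larger conditional coefficient, not from a smaller standard error.

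**Chance imbalance.** With 791/3 ≈ 264 children per arm, the share aged 4 differs between two arms by at most 1.96 × √(2 × 0.25/264) = 8.5 points (95%). Multiplied by the 6.4-point risk gap (28.2 − 21.8), this is about 0.5 points. The unadjusted 95% half-width of the contrast is 1.96 × √(2 × 0.109/264) ≈ 5.6 points and already contains that component. Removing it leaves √(5.64² − 0.55²) = 5.62.

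**The case against.** The best reply is that age may not be excluded at all. The list is introduced by the verb *include*, the article condenses a fuller protocol, and the list does not name the study arm either, although the Abstract says the model estimates the intervention effects. So the list is plainly not complete, and this stands as a real doubt. Against it, the background group names both parents' education separately and carries no open-ended marker, so a reader cannot tell that age is meant. Naming it removes the doubt.

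The second reply is that the gradient is weak evidence for this outcome. It is cumulative child-level prevalence over two years, not incidence on sound surfaces within the enrolled range. That stands, and it is why carrying it over is labelled an assumption. Caries experience is also a listed covariate and, as dmfs, the stratification factor, so part of any age effect is already carried.

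Three stronger readings are tempting and not supported:

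- *That precision is materially lost.* A gain of 5% to 9% in variance needs 30-month risks 15 or 20 points apart between the two ages (0.15²/4/0.109 = 5%; 0.20²/4/0.109 = 9%). The documents give no such gap; the quoted prevalence rises by (55 − 38)/2 = 8.5 points a year.
- *That the treatment contrast is biased because age is not stratified.* Allocation is randomised, and chance imbalance is already in the standard error.
- *That a needed behaviour item was dropped.* The Questionnaire Survey collects "oral hygiene practice, use of fluoride agents, dental visit behavior, snacking habits, parental educational level, and family income" and the model list omits the first item. But occlusal plaque and overall oral hygiene are listed, so adding reported practice is a preference.

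**Conclusion.** The point holds as a small, free improvement. Age is not among the named covariates although it is known for every child and has the only caries gradient the protocol quotes. The effect on the trial's main question is close to nil: no bias in the treatment comparison, and about 0.3 points of power on the quoted gradient. The effect on the risk-factor results is modest, at about 3% on the caries-experience ratio (1.6% to 8.9% over the range tried). Distortion of the behaviour coefficients is possible, but the documents give nothing from which to size it. These figures rest on the assumed equal age split and on the assumed transfer of prevalence to incidence. The sample size is unaffected.

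**What to change.** In Data Analysis, add age at baseline, in months, to the independent variables of the 30-month model, and state that it is prespecified and stays in the model whatever backward elimination does with the others. The cost is one model term and one line of text. No new data are needed, provided the date of birth was recorded when age eligibility was checked; if only whole years are held, use those. The unadjusted chi-square comparison and the sample size need no change.
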